#### Phase 2: Longitudinal Cohort Study

##### Participants

This cohort will consist of transgender women undergoing facial feminization surgery at the San Juan de Dios Hospital in Santiago, Chile. Participants eligible for the longitudinal cohort study phase must meet the predefined inclusion criteria, as presented in Textbox 1.

Inclusion criteria.Self-identified transgender women aged ≥18 yearsCurrently enrolled in the gender program at San Juan de Dios HospitalClinical indication for facial feminization surgery, including but not limited to genioplasty, mandibular reshaping (angle and basilar crest modification), frontal-nasal-orbital complex remodeling, rhinoplasty, and zygomatic-malar complex remodelingAbsence of craniomaxillofacial syndromes or contraindications to surgeryCompletion of a multidisciplinary evaluation by a psychologist and a social worker, confirming psychological and emotional readiness for surgeryWillingness to undergo pre- and postoperative cone beam computed tomography scans and standardized facial photographyProficiency in Spanish (speaking, reading, and comprehension)Capacity and willingness to provide written informed consent.

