The surgery involves modifications to both hard and soft tissues, which can be assessed using cone beam computed tomography (CBCT) and standardized clinical photography. The international literature identifies the frontal-naso-orbital complex (including the forehead, supraorbital crest, frontomalar prominence, temporal ridges, and frontonasal transition) and the mandibular region (chin, mandibular body, angle of the mandible, ascending ramus, and basilar ridge) as the primary anatomical determinants of facial gender. Secondary regions of importance include the nose, zygomatic region, and thyroid cartilage [1,8,15,16]. However, there is a lack of local data in Chile describing the frequency and extent of surgical modifications to these anatomical regions.

Cephalometric differences between male and female facial structures are influenced by biological sex, ethnic background, and genetic inheritance. Typically, male faces have larger craniofacial dimensions, more acute nasolabial angles, and more obtuse mandibular angles, while female face exhibit more convex profiles, smaller nasal dimensions, and less prominent chins [8,15-19].

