##### Sample Size Calculation for Cohort Study

The gender program at San Juan de Dios Hospital currently includes 70 transgender women undergoing hormone therapy and attending regular medical follow-up appointments. On the basis of this population size, a sample of 30 participants was calculated using a 95% confidence level and an estimated margin of error of 12%. This adjustment reflects logistical and ethical considerations related to long-term follow-up while maintaining sufficient statistical validity for exploratory analyses of surgical outcomes.

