###### Cephalometric and Photometric Analysis

Facial morphological changes will be measured pre- and postoperatively using CBCT, an imaging software, and extraoral pictures taken in a frontal and lateral view. The following parameters will be assessed: forehead inclination, true vertical distance, nasofrontal angle, mandibular angle, mandibular plane angle, facial profile, nasolabial angle, mentolabial angle, and mentocervical angle.

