##### Data Analysis for the Cohort Study

Descriptive statistics will be used to summarize sociodemographic variables (absolute and relative frequencies). The Shapiro-Wilk test will assess the distribution of continuous variables. Normally distributed variables will be reported as mean and SD; nonnormally distributed variables will be reported as median and IQR. Pre- and postoperative comparisons of continuous variables will be made using paired *t* tests or Wilcoxon signed-rank tests, as appropriate. Categorical variables will be compared using Pearson chi-square or Fisher exact test. Linear regression models will evaluate the associations between cephalometric and photometric changes and perceived femininity scores. Statistical significance will be set at *P*≤.05. All analyses will be conducted using Stata (version 11; StataCorp).

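### The regions operated on probably differ between women, yet the nine facial parameters are analysed with no reference to region, and none of the nine describes the zygomatic region

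*Protocol article*

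**What the plan says.** Eligibility for the cohort (Phase 2, Participants, Textbox 1) requires a clinical indication for facial feminization surgery, "including but not limited to genioplasty, mandibular reshaping (angle and basilar crest modification), frontal-nasal-orbital complex remodeling, rhinoplasty, and zygomatic-malar complex" remodeling. The list is open, and no set of procedures is required of every woman.

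The Background names the frontal-naso-orbital complex and the mandibular region as the primary determinants of facial gender. It then adds: "Secondary regions of importance include the nose, zygomatic region, and thyroid cartilage". It also notes that "there is a lack of local data in Chile describing the frequency and extent of surgical modifications to these anatomical regions".

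Morphological change is one of the three primary domains in the section Longitudinal Cohort Study. The section Cephalometric and Photometric Analysis fixes nine parameters: "forehead inclination, true vertical distance, nasofrontal angle, mandibular angle, mandibular plane angle, facial profile, nasolabial angle, mentolabial angle, and mentocervical angle". None is linked to a procedure or region.

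The section Data Analysis for the Cohort Study says: "Pre- and postoperative comparisons of continuous variables will be made using paired" *t* tests or Wilcoxon signed-rank tests. Linear regression then relates morphological change to perceived femininity. Neither analysis is restricted, stratified or adjusted by the region operated on.

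**The concern.** A parameter can be changed by surgery only if a region that bears on it is operated on. If some women have a given region left alone, their change on its parameters is mainly measurement noise and time. Pooled with the others, they pull the mean change towards zero. The reported figure then depends on how many women had that region operated on as well as on what the surgery achieved. A null result could mean that surgery had little effect there, or only that few women had it.

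The second problem is a gap in measurement. One of the five named procedures acts on a region that none of the nine parameters describes. Femininity gained from it would have no region-specific morphological predictor in the regression. The hypothesis in Objectives of the Study ties improvement to facial parameters moving towards female standards, so it relies on the parameters capturing what was changed.

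**Working it through.** **Plan's own figure.** The cohort size is the only relevant number: "a sample of 30 participants was calculated using a 95% confidence level and an estimated margin of error of 12"%, from a program that "currently includes 70 transgender women undergoing hormone therapy". The usual finite-population formula with p = 0.5 is n = N·z²·p·q / (e²(N−1) + z²·p·q). With N = 70, z = 1.96 and e = 0.12, it gives 70 × 0.9604 / (0.0144 × 69 + 0.9604) = 34.4, so 35 and not 30. That mismatch is a separate matter. The calculations below take n = 30 as planned.

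**Matching procedures to parameters.** The listed procedures cover the chin, the mandible, the frontal-nasal-orbital complex, the nose and the zygomatic-malar complex. The nine parameters are named for the forehead, the nasofrontal transition, the mandible (mandibular angle and mandibular plane angle), the profile, the nasolabial, mentolabial and mentocervical angles, and a true vertical distance. None is named for the zygomatic region.

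**Effect on the mean.** Let a fraction f of women have the region operated on, with mean change d in units of the SD of change in operated women. Let the mean change be 0 in the others. The whole-cohort mean is f·d. With d = 0.8 it is 0.56 at f = 70%, 0.40 at f = 50% and 0.24 at f = 30%. This scaling does not depend on any SD.

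**Effect on power.** The article gives no effect size, SD or case mix, so all of these are assumptions:
- d = 0.8, two-sided 0.05, n = 30, and a fixed number of operated women.
- The SD of change in unoperated women is a ratio r of that in operated women, with r from 1.0 to 0.1.

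The Abstract calls the paired *t* tests 1-tailed and the analysis section states no sidedness; two-sided is used here. Power in all 30 is simulated. Power in operated women alone comes from the noncentral *t* distribution with noncentrality d·√n.

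| Operated | All 30, r = 1.0 | r = 0.5 | r = 0.25 | r = 0.1 | Operated only |
|---|---|---|---|---|---|
| 30% | 21% | 34% | 45% | 51% | 56% (n = 9) |
| 50% | 50% | 70% | 78% | 81% | 82% (n = 15) |
| 70% | 81% | 90% | 93% | 93% | 94% (n = 21) |

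At 50% operated, the loss runs from 32 points (82 − 50) when unoperated women vary as much as operated women to 1 point (82 − 81) when they hardly vary. At 30% operated, it runs from 35 points (56 − 21) to 5 (56 − 51). If every woman has every region operated on, there is no loss.

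**The case against.** The article does not say that women receive different combinations, nor that all 30 enter every test. Textbox 1 is an eligibility criterion, and both steps are inferences. They are reasonable ones: the list is open, the Background treats regional frequency as unknown, and the analysis section states no restriction. They remain inferences, and the full protocol or analysis plan, not shown, may define region-specific analyses or record the procedures. The absence of a procedure field from a condensed article is not an error in itself.

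The whole-cohort mean is also a valid average for the surgical package as delivered, and the objectives ask about the surgery as a whole. This stands, and it is why the operated-region result belongs beside the whole-cohort result and need not replace it. The cohort is described as exploratory, and Anticipated Findings already concedes limited power for associations with cephalometric change.

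A reader might infer three stronger claims that the documents do not support:
- **A large, certain loss of power.** The 50% against 82% contrast requires unoperated women to vary as much as operated women. If their change is close to zero, most of the loss disappears.
- **A damaged regression.** Women with little change add spread to the predictor, which does not in itself harm the slope. Any weakening from unmeasured zygomatic change depends on an unknown number of women.
- **No parameter for mandibular-angle surgery.** The list includes both mandibular angle and mandibular plane angle.

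**Conclusion.** The point holds as a worthwhile, inexpensive improvement to one of the primary domains. It does not invalidate the planned analysis. Followed as written, the mean change per parameter is scaled by the share of women operated on in the relevant region, which the article does not give, so a null result cannot be assigned to the surgery. This rests on the regions operated on differing between women, which is probable but not stated, and on no average change where a region was not operated on. The cost in power cannot be fixed from the article: under the assumptions above it is between 1 and 35 points when 30% to 50% of women are operated on in the region.

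The zygomatic gap does not depend on case-mix figures. A listed procedure, on a region that the Background itself names as relevant though secondary, has no region-specific measure among the nine.

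**What to change.** 1. Take the procedures performed, by region, from each operative report and tabulate their frequency. This also supplies local data that the Background says are lacking.
2. Prespecify, before outcome data are examined, which regions can move each parameter. Some parameters, such as facial profile, respond to several regions.
3. For each parameter, report the pre/post change among women operated on in a relevant region alongside the whole-cohort change, with the number of women in each.
4. Add a zygomatic measure, for example bizygomatic width, on the CBCT scans and frontal photographs already part of the study, or state that this region is not measured. Preoperative images are already being collected, so the parameter set should be settled now.

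The cost is a change of wording, one field from the operative report and a little extra measurement on existing images. No imaging is added and no surgery is altered. The downside is that region-specific tests use fewer than 30 women, and for rarely operated regions they will be small.

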##### Sample Size Calculation for Cohort Study

The gender program at San Juan de Dios Hospital currently includes 70 transgender women undergoing hormone therapy and attending regular medical follow-up appointments. On the basis of this population size, a sample of 30 participants was calculated using a 95% confidence level and an estimated margin of error of 12%. This adjustment reflects logistical and ethical considerations related to long-term follow-up while maintaining sufficient statistical validity for exploratory analyses of surgical outcomes.

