**Objective:**

This study aims to (1) develop and validate a culturally appropriate quality-of-life questionnaire for transgender women undergoing facial feminization surgery in Chile, and (2) evaluate postoperative changes in quality of life, perception of facial femininity, and cephalometric and photometric parameters.

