## Discussion

### Anticipated Findings

One of the main challenges of this study lies in the complexity of its design. The development and validation of a quality-of-life questionnaire specifically tailored to transgender women in Chile presents a substantial methodological undertaking. The absence of preexisting instruments written and validated in Spanish for this population necessitated the creation of a new tool that is both culturally sensitive and contextually relevant.

The validation process involved multiple stages, including expert review, pilot testing, and large-scale field validation. A total of 216 participants were successfully recruited and completed the questionnaire, exceeding the initial target of 200. This larger sample size enhances the robustness of the psychometric analysis and increases the reliability of the findings. The use of a nonprobabilistic sampling strategy—based on community outreach, institutional networks, and social media—facilitated access to a geographically and socially diverse population but may introduce selection bias, potentially limiting the generalizability of the results to the broader transgender population in Chile.

The longitudinal cohort evaluating surgical outcomes includes 30 participants, a number determined by the eligible population currently enrolled in the gender program at San Juan de Dios Hospital. Although appropriate for exploratory analysis and reflective of real-world clinical constraints, this sample size may reduce the statistical power to detect subtle associations between cephalometric changes and psychosocial variables.

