This study has several limitations that should be considered when interpreting the results. First, participant retention during the 12-month follow-up period may be affected by emotional fatigue, life transitions, or reduced interest, potentially leading to attrition and incomplete datasets. Second, the reliance on self-reported measures for quality of life and femininity perception may introduce response bias, particularly in contexts shaped by stigma or social desirability. To minimize this potential bias, the questionnaire was designed to be completed online in a self-administered format, thereby minimizing interviewer influence and reducing the likelihood of socially desirable responding. Third, while third-party assessments are included to complement self-perceptions, evaluations of gender expression and facial aesthetics remain inherently subjective and culturally variable. Finally, although a control group of cisgender women is incorporated, normative comparisons may still influence the interpretation of femininity scores.

Despite these challenges, this study is supported by several strengths that enhance its feasibility and scientific relevance. The project is developed in a health network that serves a significant proportion of Santiago’s population, ensuring access to clinical infrastructure, a well-defined study population, and robust ethical oversight. Collaboration with civil society organizations in Santiago strengthens recruitment and fosters meaningful community engagement. To mitigate attrition risks, this study will implement participant-centered retention strategies, including regular follow-up through mobile messaging and social media to address potential geographic and logistical barriers.

Ultimately, this study is expected to make a valuable contribution to transgender health research in Latin America by addressing the critical evidence gap and introducing a validated, culturally appropriate instrument for clinical and academic use.

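### With the default p = 0.5, the stated inputs for the phase 2 cohort give 35 participants, not 30, and the calculation does not size the paired changes and regressions that phase 2 analyses

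*Protocol article*

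**What the plan says.** In the protocol article, Sample Size Calculation for Cohort Study starts from a gender program that "currently includes 70 transgender women undergoing hormone therapy and attending regular medical follow-up appointments". Taking those 70 women as its base, the section then reports that "a sample of 30 participants was calculated using a 95% confidence level and an estimated margin of error of 12" percent. It gives no expected proportion, standard deviation, effect size, power or dropout allowance, and it does not name the formula. The next sentence describes the result as an adjustment for logistical and ethical reasons, "maintaining sufficient statistical validity for exploratory analyses of surgical outcomes".

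The Objective for this phase is to "evaluate postoperative changes in quality of life, perception of facial femininity, and cephalometric and photometric parameters". Under Data Analysis for the Cohort Study, "Pre- and postoperative comparisons of continuous variables will be made using paired" *t* tests or Wilcoxon tests, and linear regression relates morphological change to femininity scores. The inclusion criteria select women with a clinical indication for surgery and confirmed readiness for it.

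The Discussion (Anticipated Findings) calls 30 "a number determined by the eligible population currently enrolled in the gender program at San Juan de Dios Hospital". It accepts that power for subtle associations may be reduced, and it warns that follow-up may suffer, "potentially leading to attrition and incomplete datasets".

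**The concern.** The sample-size section presents 30 as the result of a calculation, and that calculation is the only quantitative support for the cohort size. Two things look wrong.

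1. The stated inputs do not lead to 30 under the convention a reader would apply when no proportion is given.
2. A percentage margin of error for a finite population of 70 is the form used to size a random-sample survey of one proportion. No phase 2 aim estimates a proportion among program members, and the cohort is not a random sample of them.

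At stake is whether a reader can tell what 30 women can show. The 12% figure says nothing about the size of quality-of-life change, or the strength of association, that the study can estimate with useful precision.

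**Working it through.** **Inputs.** N = 70, 95% confidence, margin e = 0.12 and stated n = 30, all from Sample Size Calculation for Cohort Study. The expected proportion p is not stated. I assume p = 0.5, the usual default, and also vary it.

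**Step 1: try to reproduce 30.** For a proportion with finite-population correction:

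- n0 = z² p(1−p) / e² = 3.8415 × 0.25 / 0.0144 = 66.7
- n = n0 / (1 + (n0 − 1)/N) = 66.69 / (1 + 65.69/70) = 34.4, so **35**

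Other versions of the calculation, all at p = 0.5 except the Slovin formula, which has no p:

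| Version | n | Rounded up |
|---|---|---|
| n0 / (1 + n0/N) | 34.15 | 35 |
| Slovin, N / (1 + N e²) | 34.86 | 35 |
| z = 2 in place of 1.96 | 35.1 | 36 |
| No finite-population correction | 66.7 | 67 |
| One-sided z = 1.645 | 28.35 | 29 |

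The last row comes close to 30, but it corresponds to a 90% two-sided interval, not to a margin of error at 95% confidence.

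**Step 2: the margin that 30 delivers (p = 0.5).**

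- 1.96 × √[(0.25/30) × (70 − 30)/(70 − 1)] = 0.136, that is **13.6%**
- Without the finite-population correction: 1.96 × √(0.25/30) = 17.9%
- For comparison, n = 35 gives 11.8%

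**Step 3: what would have to change for 30 to come out.** Each of these, taken alone, works:

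- p of about 0.24 to 0.26 (0.205 to 0.32 gives 28 to 32)
- a margin of about 13.6%
- a confidence level of about 91.6%: z = 0.12 / √[(0.25/30) × (40/69)] = 1.73
- N of about 53: 66.69 / (1 + 65.69/53) = 29.8

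The last three contradict the stated inputs. A p near 0.25 does not, but the article does not mention it.

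**Step 4: precision on the scale of the aims.** Effects are in units of the SD of the within-person differences. The 24-completer column assumes a 20% loss (30 × 0.8 = 24); the document gives no rate.

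- 95% CI half-width = t(0.975, n−1)/√n: 2.045/√30 = 0.37; 2.069/√24 = 0.42
- Detectable paired change at 80% power and alpha 0.05: solve for d in the noncentral *t* distribution with n − 1 degrees of freedom and noncentrality d√n
- Detectable correlation, by Fisher z: r = tanh[(1.960 + 0.842)/√(n − 3)], that is tanh(0.539) for n = 30 and tanh(0.611) for n = 24

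| Quantity | n = 30 | 24 completers |
|---|---|---|
| 95% CI half-width, mean change | 0.37 SD | 0.42 SD |
| Detectable change, two-sided | 0.53 SD | 0.60 SD |
| Detectable change, one-sided | 0.47 SD | 0.52 SD |
| Detectable r, two-sided | 0.49 | 0.55 |

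Both sidedness options are shown because the Abstract specifies 1-tailed paired *t* tests, while the cohort analysis section gives only a significance threshold.

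**The case against.** The strongest reply is that 35 rests on an input the reviewer supplied. No proportion is stated, a value near 0.25 yields 30, and a condensed article may omit a value that the full protocol contains. This stands. A reader might infer that 30 cannot be obtained from the plan's inputs at all, and the document does not support that. What it supports is that 30 does not follow under the default p = 0.5, and that no other value is offered.

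A second reply is that the type of calculation is inferred, since neither a formula nor a proportion is named. That is also true, so the point is worded as an appearance. Still, no other standard formula runs on a population size, a confidence level and a percentage margin alone. Relative frequencies and chi-square or Fisher tests appear in the analysis section, but they are not the headline aims.

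A reader might also infer that the Discussion contradicts the sample-size section by giving a separate basis for 30. I would not press this. Both places appeal to the same gender program and to practical limits, so the Discussion reads as a loose restatement.

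Finally, the article labels the analyses exploratory, concedes reduced power for subtle associations and names attrition as a limitation. These caveats lower the risk that readers are misled, and they answer anyone who would conclude that the cohort is invalid or must be enlarged to 35. They do not repair the stated calculation.

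**Conclusion.** The point holds, at moderate severity. Under p = 0.5, the stated 95% confidence, 12% margin and population of 70 give 35 participants. The stated 30 is 5 fewer, and its margin is about 13.6%, which is 1.6 percentage points wider than claimed. Those two figures depend on p = 0.5.

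The mismatch with the aims does not depend on p. Even a corrected margin for a proportion would not show what 30 surgically selected women can say about paired change or regression associations. On that scale the cohort can reliably detect changes of roughly half an SD of the differences and fairly strong correlations, and less than that after attrition. That may be adequate for exploratory work, but the article should say so in those terms.

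**What to change.** In Sample Size Calculation for Cohort Study:

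1. Delete the justification by 95% confidence and 12% margin. State that feasibility sets the number at 30, in line with the Discussion.
2. Give the precision for the real estimand with 30 participants: the CI half-width, the detectable paired change and the detectable correlation from the table above. Say whether the paired tests are one-sided or two-sided, so that the detectable change quoted matches the test planned.
3. Show how these figures worsen with attrition. The 24-completer column can serve as an illustration if the 20% loss is labelled as an assumption.
4. If the margin statement is kept, state p and the formula, and correct the margin (13.6% at p = 0.5).

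The cost is wording and one slightly less favourable figure. No extra patients and no change of design are needed.
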